### Study procedures

#### Data collection

Caregivers and patients’ sociodemographic data (sex, date of birth, place of residence, matrimonial status, study level, professional status) and patients’ medical data (type of disease, stage of disease, treatment) will be collected by the CRA by interviews or from medical files and recorded via CleanWeb Designer™ software version 164.3.0 (Telemedicine Technologies SA).

#### Administration of questionnaires

Caregivers will receive the questionnaires by post or by an email inviting them to complete the questionnaires online via CleanWeb Designer™ software. Each participating caregiver will be free to choose their preferred method for completing the questionnaires. All questionnaires are self-administered. The CRA will carry out sending and receipt of questionnaires. If filled questionnaires are not received 4 weeks after sending, a follow-up call will be performed by the CRA.

A schematic diagram of time schedule for the administration of the different questionnaires is presented in Fig. 3.

**Fig. 3 Fig3:**
[figure not shown]
A schematic diagram of time schedule for enrollment, interventions, assessments and visits for participants

#### Health-related Quality of life

The primary endpoint of the study is HRQoL. This will be evaluated using the Medical Outcomes Study (MOS) Short Form (SF)-36, which is a self-administered questionnaire [22–28]. It comprises 36 items divided into eight scales, namely: physical functioning (10 items), role limitations due to physical health (four items), pain (two items), general health perceptions (five items), energy/fatigue (four items), social functioning (two items), role limitations due to emotional problems (three items), mental health (five items) and health change (one item). The average time required for completion is 5 to 10 min. It is the most frequently used generic instrument, and has been translated and validated in the French language in a wide range of diseases [29, 30]. One score is generated per dimension, and normalized on a scale of 0 (worst HRQoL) to 100 (best HRQoL). Physical and mental health summary scores are also generated.

HRQoL will also be evaluated for caregivers of cancer patients using the CareGoQoL questionnaire. This self-administered questionnaire includes 29 items assessing 10 HRQoL dimensions, namely: psychological wellbeing, burden, relationship with health care professionals, financial and administrative management, coping, physical wellbeing, self-esteem, leisure activities, social support and private life. For each individual, scores for a dimension are computed if at least half of its contributive items are answered. The score of each dimension is obtained by computing the mean of the item scores for that dimension. An index is computed as the mean of the dimension scores. All dimension scores and the index are linearly transformed and standardized on a scale of 0–100 (the higher the score, the better the HRQoL). This instrument has recently been validated in French [31].

#### Anxiety and depression

Anxiety and depression will be assessed using the self-administered Hospital Anxiety and Depression Scale (HADS) questionnaire. This includes 14 items distributed in two subscales, namely an anxiety and a depression subscale. Each item is measured on a 0 to 3 scale. The HADS has been used in various medical contexts (hospitalized and nonhospitalized patients as well as apparently healthy persons). It has also been validated in the French language [32–34].

#### Coping

The coping strategies used by caregivers for stress adaptation will be identified using the coping scale developed by Borteyrou, Truchot and Rascle [35]. It includes 25 items to assess six dimensions: escape strategies (behavioral avoidance strategies that allow caregivers to leave the care context), psychological and behavioral disengagement strategies (avoidance strategies to protect against sources of stress), positive reinterpretation strategies (cognitive strategies to distance oneself emotionally from problems encountered), distraction activities or behavioral strategies that aim to restore resources (protective strategies to leave the care context during which caregivers play an active role in entertaining or social activities), and consultations with a psychologist and seeking social support (emotional strategies that aim to verbalize problems, express negative emotions, exteriorize feelings without any obvious desire to find solutions to problems). The validity of this tool has been tested in professional caregivers and noncaregivers in oncology. This coping scale will identify the processes by which caregivers confront the stresses linked to their care relationship.

#### Social support

The six-item Short Form of the SSQ6, which is validated in French, will be used to qualitatively and quantitatively evaluate the caregivers’ social network [36, 37]. The SSQ6 is administered in two steps. During the first step, respondents indicate the name or the initials of people providing each social support described. In this way, a list of persons in the network is established. In the second step, respondents indicate, for each person, their degree of satisfaction with regard to the support received. It is possible to calculate a total score for availability *N* by adding the number of persons available for each type of support. A satisfaction score for the support provided by the network is calculated by adding scores obtained, which vary from 1 to 5 [38].

#### Caregiver burden

The Zarit Caregiver Burden Interview will be used to evaluate the burden represented by caring for a patient living at home [39]. It reveals the degree of exhaustion or psychological fatigue of caregivers. It is composed of 22 items, scored 0 to 4, divided into three dimensions: the relationship with the person being cared for, repercussions on caregivers’ life and their own emotional state. Responses are distributed on a scale of 5 points. The overall score shows whether there is a slight, moderate or heavy burden or no burden at all. In addition to evaluating the material and emotional burden, this inventory also contains a complementary questionnaire of 27 items, scored 0 to 4, centered on the evaluation of problems with the behavior and autonomy of the cared person, scored according to their frequency and the caregivers’ emotional reactions. The score sheet has two parts: one part “frequency” and one part “relationship.” The Zarit Caregiver Burden Interview is a reliable tool that has been validated in French for the assessment of caregiver burden [37].

#### Qualitative studies

The qualitative studies will make it possible to answer the secondary objectives of this research:To study the caregiver-patient relationship, we will conduct semistructured interviews with 50 caregiver-patient pairs (10 pairs in each pathology group). Interviews will be recorded and transcribed in their entirety. These interviews (between 1 and 1.5 h long) will be performed with caregivers and patients separately at baseline and every 6 months thereafter over 5 years. Analysis of the interviews will include: thematic content analysis of each interview (first level of analysis), cross-sectional analysis of the content of the caregiver/patient story (second level), cross-analysis of the narratives collected from each group of caregivers and elements of the relevant literature (third level). These analyses will characterize the predetermination of caregiving, explore the experience of helping, retracing its path and analyzing the mutual perception of the aid relationship and the difficulties encountered.To describe the specificities of the relationship when the caregiver has to face behavioral and psychological problems in the patient (Alzheimer-type dementia in particular), we will compare two groups of 25 caregivers. The first group will be caregivers of patients with dementia, and the second group caregivers of patients with cancer. This study is based on semistructured interviews and auto-administered questionnaires. We will meet each person every 6 months during the first 5 years of their role of caregivers to evaluate the following:The quality of the attachment relationship using the Relationship Scales Questionnaire (RSQ) [46]Alexithymia, using the Toronto Alexithymia Scale (TAS) [47]Negative and positive reactions to caregiving using the Caregiver Reaction Assessment [48].
To measure the “dispossession” of the caregiver role when the patient is in remission, enters an institution or dies and the repercussions of this event, and to evaluate the consequences for caregivers, we will perform, every 6 month after the event and until the end of the cohort, semidirective interviews with 90 caregivers whose patient had had a disease remission (30 caregivers), entered an institution (30 caregivers) or died (30 caregivers).

#### Analysis

Analyses will be performed using SAS (version 9.4) (SAS Institute Inc., Cary, NC, USA), R (version 3.2.2) [49] and Stata (v13) (StataCorp LP, TX, USA) software. The statistical analysis plan for the primary and secondary objectives will be written before the database is locked.

All analyses will be on a modified intention-to-treat principle, i.e., including all randomized informal carers regardless of the eligibility criteria and intervention received, with MOS SF-36 scores available at baseline and 1 year. Analyses for the interventional study will be done on an intention-to-treat basis. After Bonferroni adjustment, statistical significance will be fixed at the 0.005 level for primary analyses, and at the 0.05 level for the secondary objectives.

An interim analysis is planned when half of the patients will be included to reject or not H0 (efficacy) or H1 (futility); the Alpha Spending Function with O’Brien-Fleming Boundaries will be used to determine the alpha-level significance at the interim and at the final analysis using EAST® software (Cytel Software Corporation, Cambridge, MA, USA) [50]. The corresponding confidence interval will be computed (1 − alpha level).

Sociodemographic and clinical characteristics will be described at inclusion using frequency (percent) for qualitative variables and mean (SD), or median (min–max) for continuous variables. Data will be compared between randomization arms using the Student *t* test or the nonparametric Mann-Whitney test, or analysis of variance (ANOVA) or the Kruskal-Wallis test for continuous variables and the Chi-squared or Fisher’s exact tests for qualitative variables, as appropriate. Scores will be described at each follow-up time point using mean (SD) and median (min–max) in each arm.

After describing missing data and investigating the mechanism of missing data profiles, imputation will be performed using a multiple imputation method by sensitivity analysis after checking normality, and univariate and multivariate ANOVA adjusted for baseline score will be performed to compare the two summary scores of the SF-36 questionnaire at 1 and 2 years.

Multivariate analyses will be performed including at least the stratification criteria for randomization, as well as variables associated with HRQoL at the 10 % level by univariate analysis. HRQoL data will also be longitudinally analyzed using a mixed model of analysis of variance for repeated measures (or pattern mixture models in case of a missing-not-at-random profile) in order to test an arm effect, time effect and an interaction between arm and time, as well as the effect of other relevant parameters (HADS, coping, clinical parameters, etc.). Some random effects on patients will also be introduced into the model in order to reflect individual trends. Burden, coping and HADS will also be modeled as time-dependent covariables in another model. Time to HRQoL score deterioration will be estimated using the definitions of both Bonnetain et al. [51] and Hamidou et al [52]. Item Response Theory, cluster analyses, structural equation modeling as well as classical factorial analyses will be conducted as complementary analyses to define and validate longitudinal profiles of caregivers. All these analyses will be repeated in each subgroup defined by stratification (including cancer localizations) for sensitivity analyses.

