#### Interventional study

A randomized interventional trial in a 1:1 ratio will be conducted within this cohort to evaluate the effect of a pragmatic supportive intervention on caregivers, provided by a social worker and an information booklet (intervention arm) versus the control arm, where caregivers will only receive the information booklet, without social worker support. The intervention will be conducted during the first 2 years of entrance into the caregiver’s role. The intervention proposed here mobilizes social workers of the Departmental Councils, of the General National Retirement Fund (CARSAT Burgundy-Franche-Comté) and of the Community Social Action Association (CCAS of Dijon). All institutions providing social workers are officially involved in the study and all social workers are trained in the management of older people, characteristics of caregiving relationships and in ICE cohort study procedures. The structure and purposes of the social worker’s intervention are described in Table 1. The main objective is to compare the mental and physical health summary scores on the MOS SF-36 at 1 year between the two groups. Secondary objectives are to compare the following parameters between groups: (1) the mental and physical health summary scores of the MOS SF-36 at 2 years, (2) all HRQoL dimensions of the MOS SF-36 at 1 year and at 2 years, (3) longitudinally: all HRQoL dimensions of the MOS SF-36 and the CarGOQoL questionnaire (only for caregivers of the cancer patient group), (4) coping strategies (as assessed by the coping scale developed by Borteyrou, Truchot and Rascle [35]), (5) anxiety-depression (as assessed by the HADS), (6) social support (as assessed by the SSQ6) and the perceived caregiver burden (as assessed by the Zarit Caregiver Burden Interview) and (7) to assess from a societal perspective the incremental cost-effectiveness ratio (ICER) of the intervention of a social worker for caregivers. The ICER will be expressed in terms of quality-adjusted life years (QALYs) gained based on a utility score that will be calculated based on the EuroQoL EQ-5D questionnaire, the SF-6D which is composed of 11 items of the SF-36 questionnaire and the Center for Epidemiologic Studies-Depression Scale (CES-D) questionnaires and economic survey.

**Table 1 Tab1:** Content and purposes of the pragmatic intervention by a social worker in the intervention group of the nested randomized trial for caregivers

Format of the intervention:

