For each caregiver randomized to the intervention arm of the trial, a social worker will conduct an individual interview with the caregiver
Purposes of the interview:
To simply listen to the caregiver and allow them to express their complaints (and to be attentive to unspoken complaints) To evaluate the level of difficulty experienced by the caregiver in their daily routine, being attentive to their personal situation To respect and respond to any needs and/or requests expressed by the caregiver, and provide active support; guarantee confidentiality of the conversations and ensure that the caregiver participates willingly, without intruding in their life To provide any resources that are lacking in the caregiver-patient relationship; provide information about available solutions for respite care, and other solutions specific to each case (accommodation, health care pathway, logistic/material support for the caregiver/patient) To help the caregiver to more quickly apprehend and come to terms with their commitment of being a caregiver To be attentive to any alert signals and prevent deterioration towards crisis situations (burn-out, abuse); to alert third parties if the caregiver is found to be in a critical situation Through their interactions with the caregiver, the social worker will provide accompaniment and support, offering pertinent information and orientation towards appropriate structures of care depending on the situation the caregiver describes. The intervention leaves it to the discretion of the social worker to decide what is the most appropriate way to operate and the most appropriate solution to propose in practice for each caregiver The intervention also aims to determine whether the needs expressed by the caregivers vary according to the patient’s disease, or according to the patient’s age, sex or place of residence. After the intervention, the social worker will complete a standardized Data Transmission Sheet, with the Linear Analogue Scale Assessment quality of life (LASA) questionnaire (about the caregiver but completed by the social worker), to be forwarded to the study coordinator. They will receive receipt of their submission once the forms have been submitted

The duration of patients’ and caregivers’ participation in the cohort study is 5 years. The entire cohort study’s duration is 10 years: 5 years of inclusions and 5 years of follow-up. Only the interventional study is restricted to 2 years.

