With a bilateral alpha risk of 5 % and a statistical power of 90 % to detect a difference of at least 5 points (standard deviation (SD) = 25), and adjusted to take account of the number of statistical tests and maintain an overall alpha type one error rate of 5 % (Bonferroni adjustment):With two dimensions of HRQoL, α’ = α/2 = 0.05/2 = 0.025With five groups of diseases, α” = α’/5 = 0.025/5 = 0.005 (cancer (breast, prostate, colorectal); neurodegenerative disease (Alzheimer’s disease and similar diseases); AMD; neurovascular (stroke); cardiac (heart failure))At least 1684 caregivers should be randomized in each disease group. However, we anticipate lower recruitment in the heart failure group. Accordingly, only 488 caregivers will be randomized (bilateral α type I error of 0.005 and statistical power of 80 %) to demonstrate a difference of at least 5 points (SD = 15). Thus, it will be necessary to include and to randomize 4 × 1684 = 6736 caregivers, plus 488 in the heart failure group, representing a total of 7224 caregivers. An interim analysis will be planned to reject either H0 or H1 (Alpha Spending Function and O’Brien-Fleming Boundaries) when half the caregivers have been included with 1 year of follow-up in each of the subgroups. To allow for 5 % of loss to follow-up, it will be necessary to include and randomize an additional 380 caregivers, resulting in an overall total of 7604 caregivers (1750 caregivers for each of the four large groups of diseases and 604 for the heart failure group)

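### The analysis plan is due only before database lock, so the parts of the primary analysis still open may be settled after the interim comparison by arm

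*Protocol article*

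**What the plan says.** All places are in the protocol article.

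- **Deadline for the plan** (Analysis): "The statistical analysis plan for the primary and secondary objectives will be written before the database is locked". No other date is given, and nothing links the plan to the interim analysis.
- **Interim analysis** (Analysis): "An interim analysis is planned when half of the patients will be included to reject or not H0 (efficacy) or H1 (futility". The sample size section places it "when half the caregivers have been included with 1 year of follow-up in each of the subgroups".
- **Boundaries** (Analysis): alpha spending with O'Brien-Fleming boundaries "will be used to determine the alpha-level significance at the interim and at the final analysis".
- **Primary comparison** (Interventional study): "The main objective is to compare the mental and physical health summary scores on the MOS SF-36 at 1 year between the two groups". The interim look therefore uses the primary endpoint at its primary time point.
- **Level** (Analysis): "statistical significance will be fixed at the 0.005 level for primary analyses", from 0.05 divided by two scores and five disease groups, so ten tests.
- **Duration** (end of the Interventional study section): the whole cohort's "duration is 10 years: 5 years of inclusions and 5 years of follow-up".

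The Analysis section also leaves three features of the primary test unsettled:

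- **Analysis set.** One sentence puts all analyses on a modified intention-to-treat set, requiring SF-36 scores at baseline and 1 year. The next puts the interventional study on intention-to-treat.
- **Model.** Both univariate and multivariate ANOVA adjusted for baseline are announced for the two summary scores, and neither is named as primary.
- **Covariates.** The multivariate analyses take the stratification factors as a minimum, then add variables that pass a 10% univariate screen against quality of life.

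**The concern.** Writing the plan before lock protects a trial with a single look at the end, because nobody has compared the arms by then. This trial compares them earlier. A plan written after the interim analysis would comply with the protocol, yet its authors could know which analysis set, model or covariates had favoured the intervention at half information.

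Two things are at stake. The 0.005 level holds only if the choice of test does not depend on the results. And the O'Brien-Fleming calculation assumes that the interim and final statistics come from the same analysis. If the plan follows the interim, the two may differ.

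This is not a complaint that plan details are absent from an article. The article states a deadline, and that deadline is too late for a design with an interim comparison.

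**Working it through.** **1. The plan's own figures.** Per arm, n = 2(SD/δ)²(z₁₋α/₂ + z₁₋β)², with two-sided α = 0.005 (z = 2.807).

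- Four large groups, designed "to detect a difference of at least 5 points (standard deviation (SD) = 25" with 90% power: 2 × (25/5)² × (2.807 + 1.282)² = 835.8, so 836 per arm and 1672 in total. The article states 1684 (+0.7%).
- Heart failure, 5 points, SD 15, 80% power: 2 × (15/5)² × (2.807 + 0.842)² = 239.6, so 240 per arm and 480 in total. The article states 488 (+1.7%).
- 4 × 1684 + 488 = 7224, as stated.

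The design is thus sized for ten tests at 0.005 each. The timing of the plan changes none of these numbers.

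**2. Where the decision falls.** I used O'Brien-Fleming-type spending at information fraction 0.5 and two-sided α = 0.005.

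- Interim: α₁ = 2[1 − Φ(2.807/√0.5)] = 0.00007, so |Z| > 3.97.
- Final: |Z| > 2.81, nominal p = 0.00497.
- Chance of crossing the interim efficacy boundary if the 5-point effect is true, large groups (842 per arm): the final mean Z is 5/(25√(2/842)) = 4.10. At half information it is 4.10 × √0.5 = 2.90, so the chance is 1 − Φ(3.97 − 2.90), about 14%.
- Heart failure (244 per arm): the final mean Z is 5/(15√(2/244)) = 3.68, which gives about 9%.

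Most efficacy conclusions will therefore rest on the final test, whose open features could be settled after the interim.

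**3. Length of the window.** Even accrual is my assumption. Half are included at year 2.5 and have 1-year data at 2.5 + 1 = 3.5 years. The last 1-year outcome arrives at 5 + 1 = 6 years. The gap is at least 6 − 3.5 = 2.5 years, and 10 − 3.5 = 6.5 years if lock means the end of the cohort. The article does not date the lock, and accrual by disease group may differ.

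**4. Illustration of the error rate.** None of these inputs is in the article:

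- K candidate analyses with equally correlated z statistics
- ten independent tests, all null
- no early stopping
- one variant chosen for all ten tests on interim data at half information
- final test at |z| > 2.807

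With no selection, familywise error is 1 − 0.995¹⁰ = 4.9%, within the 5% Bonferroni bound. Two million simulated null trials per row gave:

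| K | Correlation | Chosen by summed \|z\| | Chosen by single largest \|z\| |
|---|---|---|---|
| 2 | 0.80 | 5.8% | 6.4% |
| 2 | 0.90 | 5.5% | 6.0% |
| 2 | 0.95 | 5.4% | 5.7% |
| 4 | 0.80 | 6.7% | 8.1% |
| 4 | 0.90 | 6.1% | 7.1% |
| 4 | 0.95 | 5.7% | 6.4% |

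Other runs put the low end nearer 5.2%, so I quote about 5.2 to 8.1%.

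**5. One-sided view of a single test.** If the variant most favourable to the intervention is chosen for that test, the false-positive rate in its favour rises from 0.0025. It becomes 0.0032 to 0.0038 with K = 2, and 0.0038 to 0.0055 with K = 4 (correlation 0.95 to 0.80).

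**The case against.** The strongest reply is that the deadline is only an outer limit. It permits a late plan without requiring one, and the boundary family and software for the interim are already named, so part of the interim plan exists. Lock might also be meant to include a lock for the interim data. The article condenses a fuller protocol, which may date the plan and restrict access to interim results. All of this is fair. It means the article does not show that the plan will follow the interim. It does not change the rule as stated, which such a plan would satisfy. If an interim lock is meant, the sentence should say so.

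A reader might infer that the whole primary analysis is open. It is not. Both SF-36 summary scores, the 1-year time point, baseline adjustment, the 0.005 level, the boundary type and the minimum covariates are fixed. Multiple imputation is labelled a sensitivity analysis, and the longitudinal models are additional. With 5% planned loss, the two analysis sets would overlap by about 95%, so variants that differ only in the set would be highly correlated.

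A reader might also infer that final results would be known when the plan is written. Only interim results, on about half the data, need be known. No blinding is described, but knowing individual allocations is not the same as knowing results by arm.

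Finally, an earlier date alone does not cure the 10% covariate screen, which depends on the data whenever the plan is signed. That point stands, and the fix must name the covariates.

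**Conclusion.** The concern holds in a limited form. The article sets a deadline that allows the analysis set, the primary model and the additional covariates to be settled after the arms have been compared on the primary outcome. The interim and final tests therefore need not be the same pre-specified test.

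The harm cannot be read off the documents. With two to four variants correlated at 0.80 to 0.95, and one common choice made on interim results, familywise error is about 5.2 to 8.1% instead of 5%. The number of variants, their correlation, the independence of the ten tests and the deliberate selection are all assumed.

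A larger figure is tempting. Choosing the best of four variants separately for each test gives 0.0078 to 0.0108 per test, and ten times that is 7.8 to 10.8%. That would need up to ten different primary models, whereas the article describes one plan and one analysis for all groups. It should not be used.

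This should be fixed. It is not a must-fix, because no stated figure is wrong, the main elements are already fixed, and a late plan is permitted but not prescribed.

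**What to change.** Replace the sentence on the plan's timing in the Analysis section with:

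> The statistical analysis plan, naming one analysis set, one primary model with pre-specified covariates, and the interim boundaries, will be finalised, signed and dated before the first interim analysis in any disease group and before any outcome is summarised by arm; later changes will be reported as post hoc.

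The cost is an earlier writing date. No participants, data or visits are added, and the sample size does not change. It must be done before the first disease group reaches its interim analysis, because the protection cannot be recovered once results by arm have been seen.

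### The Analysis section names two incompatible analysis sets for the trial, and the modified intention-to-treat rule turns the primary comparison into a complete-case analysis

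*Protocol article*

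**What the plan says.** The Analysis section sets the population in two consecutive sentences. The first reads "All analyses will be on a modified intention-to-treat principle" and defines the set as "including all randomized informal carers regardless of the eligibility criteria and intervention received, with MOS SF-36 scores available at baseline and 1 year". The second reads "Analyses for the interventional study will be done on an intention-to-treat basis".

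Other parts of the protocol article bear on this:

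- **Endpoint** (Interventional study): "The main objective is to compare the mental and physical health summary scores on the MOS SF-36 at 1 year between the two groups".
- **Timing of baseline** (Randomization procedure): carers are randomised once their inclusion questionnaires have been completed and collected.
- **Primary comparison** (Analysis): "univariate and multivariate ANOVA adjusted for baseline score will be performed to compare the two summary scores" at 1 and 2 years.
- **Missing data** (Analysis): after the missing-data mechanism has been examined, "imputation will be performed using a multiple imputation method by sensitivity analysis after checking normality".
- **Longitudinal analysis** (Analysis): "HRQoL data will also be longitudinally analyzed using a mixed model of analysis of variance for repeated measures", with pattern mixture models if data are missing not at random.
- **Contact by arm** (Randomization procedure): social-worker visits are scheduled every 6 months, from month 6 to month 24, in the intervention arm only. Control carers receive the booklet and may approach the social services themselves.
- **Timing of the plan** (Analysis): the statistical analysis plan is to be written before database lock, and an interim efficacy and futility analysis is planned at half inclusion.

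**The concern.** An intention-to-treat set contains every randomised carer. A set that requires a 1-year SF-36 contains only those who answered at 1 year. A statistician who follows one sentence breaches the other, and the choice affects the primary test in each of the five disease groups.

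If the modified rule is followed, inclusion depends on an event after randomisation, namely that the outcome was observed. A carer may fail to return the 1-year questionnaire because of exhaustion or illness, or because the patient has died or entered an institution. The protocol itself anticipates burn-out, nursing home placement and death. If such losses differ between arms in number or kind, the comparison of completers is no longer protected by randomisation. The significance level is strict (0.005 per test), so even a modest shift matters in relative terms.

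The interim analysis adds urgency: the set could still be unsettled when the first comparative results are seen.

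**Working it through.** **1. Can the two sentences be reconciled?**

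- One could assign the modified rule to the cohort and intention to treat to the trial. But the first sentence covers every analysis, and it defines its set by randomisation and by intervention received, which are trial terms.
- One could read the second sentence as meaning only that carers are analysed in the arm assigned. Then the first sentence still fixes the set as those with both scores.
- Neither reading gives an all-randomised primary set without overriding one of the sentences.

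**2. Which condition has effect?** Baseline questionnaires are collected before randomisation, so nearly every randomised carer should have a baseline score. What remains is the 1-year score, which is the primary endpoint. The rule is therefore a complete-case rule.

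**3. Consistency with the rest of the section.** If the rule applied literally to every analysis, no 1-year score would be missing, so multiple imputation would have none to fill in. Carers with a 2-year or other score but no 1-year score would also leave the 2-year and longitudinal analyses. Both consequences conflict with the planned imputation and the mixed or pattern mixture models.

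**4. The plan's own sample size** (Sample size calculation section; normal approximation, two-sided alpha 0.005, z = 2.807):

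- Large groups, difference 5, SD 25, power 90 %: 2 × (2.807 + 1.282)² × 25²/5² ≈ 836 per arm, or 1672 in total, against 1684 stated.
- Heart failure, difference 5, SD 15, power 80 %: 2 × (2.807 + 0.842)² × 15²/5² ≈ 240 per arm, or 480, against 488 stated.
- Total with 5 % loss: 7224/0.95 ≈ 7604, as stated.

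These figures reproduce closely and are not in dispute.

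**5. Power under the modified rule.** In a large group of 1750 with 5 % missing, about 1662 carers are analysed and power is 89.8 %. It is 87.7 % at 10 % missing and 82.5 % at 20 %. At the planned loss the issue is bias, not power.

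**6. Bias.** Let p₁ and p₀ be the proportions without a 1-year score in the intervention and control arms. Let g be the mean score of completers minus that of non-completers, taken as equal in both arms. In each arm, the mean of all randomised carers equals the completer mean minus p × g. So

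bias of the unadjusted completers' difference = g × (p₁ − p₀).

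The document gives neither loss by arm nor g, so the values below are assumptions:

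| Missing, intervention vs control | g (points) | Size of bias (points) | Type I error (nominal 0.005) |
|---|---|---|---|
| 5 % vs 5 % | 5 to 15 | 0 | 0.005 |
| 5 % vs 10 % | 5 | 0.05 × 5 = 0.25 | 0.006 |
| 5 % vs 10 % | 10 | 0.05 × 10 = 0.50 | 0.009 |
| 5 % vs 10 % | 15 | 0.05 × 15 = 0.75 | 0.014 |

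The type I error uses 875 carers per arm before loss and SD 25. For 5 % vs 10 % missing, the standard error is 25 × √(1/831.25 + 1/787.5) ≈ 1.24. A 2.5 % vs 7.5 % split, which keeps the planned 5 % overall loss, gives the same bias because only the difference enters the formula.

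On sign: if visits retain intervention carers (p₁ < p₀) and non-completers score worse (g > 0), the bias is negative and hides benefit. The opposite pattern of loss would favour the intervention.

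**The case against.** The strongest defence is that the plan already takes missing data seriously. It examines the mechanism, imputes, and fits mixed or pattern mixture models, so the restriction was probably meant only for the 1-year comparison. Questionnaires go out by post or email, and the research assistant chases them after 4 weeks, with no difference stated between arms. Planned loss is only 5 %. The comparison adjusts for baseline score, and a baseline-adjusted complete-case analysis is valid if missingness depends only on arm and modelled covariates. Much of this stands, and it limits the size of the problem. It does not remove the conflict between the two sentences, and none of the planned remedies is named as primary.

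A reader might infer more than the document supports:

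- **That carers without a 1-year score are certainly dropped from the 2-year, longitudinal and cohort analyses.** This follows only from a literal reading, which sits badly with the planned imputation and mixed models. It is an ambiguity to close, not an established exclusion.
- **That only one arm can have social-worker contact before 1 year.** Only scheduled visits are confined to the intervention arm. Control carers may seek support from the same services.
- **That time to deterioration suffers immortal-time bias.** The definitions are given only by citation, so how death or withdrawal is counted cannot be seen.
- **That the bias could reach 2 points, 40 % of the target.** That needs a 20-point gap and a 10-percentage-point difference in loss. With 5 % loss overall and 1:1 allocation, this means 0 % versus 10 %, the most extreme split possible. It also ignores the baseline adjustment.

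**Conclusion.** The concern holds in this form. The Analysis section contradicts itself on the trial's analysis set, and following the modified intention-to-treat sentence makes the primary 1-year comparison a complete-case analysis selected after randomisation. That conclusion rests on the text alone and is firm.

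The size of any bias is not derivable from the document. Under the assumptions shown it lies between zero and 0.75 points, or up to 15 % of the 5-point target (0.75/5), before baseline adjustment, which would reduce it. That loss differs by arm is plausible, given the scheduled visits in one arm, but it is not shown. The point should be settled before the interim analysis because it decides who enters the primary test.

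**What to change.** Before the interim analysis, amend the Analysis section, and carry the same wording into the statistical analysis plan, so that:

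1. There is one primary set: all randomised caregivers, analysed in the arm assigned.
2. The primary analysis accommodates missing 1-year scores. It is either a likelihood-based repeated-measures model using whatever SF-36 assessments are scheduled up to 1 year, or multiple imputation. The SF-36 schedule must be confirmed first: the schedule figure is not shown, and the 3-monthly questionnaires in the Efficiency section are not clearly stated to include the SF-36. If no SF-36 falls between baseline and 1 year, the repeated-measures model gains little over the completers' comparison, and multiple imputation with auxiliary variables is the more useful choice.
3. The set with both baseline and 1-year scores is kept as a sensitivity analysis.
4. The 1-year-score condition is stated not to apply to the 2-year, longitudinal, time-to-deterioration or cohort analyses.

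The cost is a change of wording and slightly more analysis work. No new data and no change in sample size are needed.
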